#### Magnetoencephalography (MEG)

Participants will be seated inside a magnetically shielded room (VACOSHIELD, Vacuumschmelze GmbH & Co. KG, Hanau, Germany) with their heads positioned within the sensor array of the whole-head-MEG System (Elekta Neuromag TRIUX, Elekta Oy, Helsinki, Finland), consisting of 204 planar gradiometers and 102 magnetometers. MEG data will be acquired at 1000 Hz and band-pass filtered (0.1–330 Hz).

##### Subject preparation

Five head position indicator (HPI) coils will be attached to the participant’s scalp to measure and follow head position with respect to the MEG sensors. Positions of the HPI coils, three anatomical landmarks (nasion, left and right preauricular points), and ~ 150 additional points on the head surface will be determined with a Fastrak 3D digitizer (Polhemus, Vermont, USA). Vertical and horizontal electro-oculograms will be recorded with two pairs of electrodes. The first pair is placed above and below the right eye and the second pair lateral to the outer canthi of the eyes. Electrocardiography will be recorded with a pair of electrodes placed 3–5 cm bellow right and left clavicle and with 8–12 cm inter-electrode distance. The ground electrode will be placed on the right clavicle. EMG activity will be recorded from Sol, MG and TA muscles (EMG setup 3).

##### Equipment

Two custom-made MEG-compatible devices (University of Jyväskylä, Jyväskylä, Finland) were utilized in the study: a pneumatic ankle-movement actuator and a dynamometer capable of measuring isometric ankle plantarflexion and dorsiflexion forces. The chair was modified by removing its shank and foot support and installing a metallic rail (aluminum and brass) to allow adjustable attachment of both equipment to it.

The pneumatic ankle-movement actuator was adapted from the device made by Piitulainen et al. [116]. The operating principle of the MEG compatible pneumatic actuators is reported in Piitulainen et al. [117]. In brief, the actuator is composed of four pneumatic muscles (DMSP-10-120 N-AM-CM, Festo, Vantaa, Finland) embedded into a plastic and aluminum frame with a rotating platform that supports the participant’s foot. The rotation occurs in the sagittal plane (i.e. ankle dorsiflexion) when the internal pressure of the pneumatic muscles is increased (from 1 to 7 bar) and returns to the initial position when the air pressure is released. Rotation axes of the actuator and ankle joint can be aligned. The foot is fixed to the rotating platform by a strap passing firmly around the forefoot.

The isometric dynamometer composed of a metallic plate in L format, with a hard foam support for the posterior distal shank and for the heel. An adjustable metal attachment is positioned on the person’s forefoot. The shank-support is embedded with a load cell and has a strap to fasten the shank, enabling it to measure isometric knee extension and flexion forces. Another load cell is embedded in a support part holding the adjustable metal attachment. A strap firmly secures the participant’s forefoot and thus the load cell can measure both isometric ankle plantarflexion and dorsiflexion forces.

##### MEG protocol

Before the participant enters the shielded room, a 5-min empty room measurement will be recorded to estimate intrinsic noise levels of the MEG sensors for the needs of later data analysis. Three experimental MEG tasks will be performed in the following order: (1) resting state, (2) proprioceptive stimulation and (3) isometric muscle action. The resting-state task consists of two 5-min recordings, in which the participant will remain relaxed fixating on a cross on a screen positioned 1 m away from the participant’s eyes. In the proprioceptive stimulation, the pneumatic ankle-movement actuator will evoke a total of 100 dorsiflexions (movement range from 0° to ~ 15°) with a moderate velocity (mean: 15°/s; peak: 35°/s) every 4 s with ±0.2 s random jitter between the consecutive stimuli. Participants will be instructed to relax and not to resist the movement, fixate on the fixation cross, and avoid excessive eye and head movements. The view of the foot and actuator is blocked, and Brownian noise will be played through earplugs in an individually adjusted volume to mask the noise generated by the movement actuator. In the third task, first a preparatory activity of ten 2-s isometric dorsiflexions with increasing intensity (i.e. ~ 20 to 90% of MVC) at 0° ankle angle in the ankle dynamometer will be performed. Then, in the same position, three to five maximum isometric dorsiflexions (~ 3 s each) will be performed, followed by four sets of submaximal isometric dorsiflexions at 10% of MVC with 120 s of duration each. Visual torque feedback will be provided in real-time, and participants will be instructed to maintain as stable as possible torque throughout each submaximal trial. To avoid fatigue, 1–2 min of rest periods will be enforced between trials (except in the preparatory activity). If the participant is unable to perform dorsiflexion adequately, plantarflexion will be used. Continuous HPI tracking will be performed for later correction of head movements.

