### Study purpose

The present study has three aims: 1) to investigate the effects of the EXECP intervention on the following variables: gait performance (primary outcome), physical activity level, lower limb muscle strength and joint flexibility, gross motor function, cardiometabolic risk factors, neuromuscular parameters for triceps surae muscle, cortical processing of proprioceptive stimuli evoked by passive ankle dorsiflexions, tibialis anterior (TA) cortico-muscular and intramuscular coherence; 2) to evaluate the retention of the adaptations induced by the intervention after three months; 3) to compare CP and typically developing (TD) individuals in all studied variables using group and matched (age/sex) individual data. The EXECP intervention is composed of a three-month individually tailored exercise intervention containing strength training targeting lower limb and trunk muscles, combined with stretching of diagnosed short muscles and gait training. The primary hypothesis is that the EXECP intervention will enhance gait performance by: a) increasing walking distance in the 6 min walking test; b) increasing ankle dorsiflexion during the swing and stance phase of gait; c) increasing maximal walking velocity, joint net moments and ranges of motion in the lower limb joints. The secondary hypothesis are that the EXECP intervention will: d) increase habitual PA; e) increase maximal isometric and concentric torque and rate of force development for the trained muscles; f) not affect cardiometabolic risk factors such as arterial stiffness, insulin resistance, blood lipids and body fat content; g) increase gross motor function measure (GMFM; [19]) score; h) increase lower limb joint flexibility of the trained muscle groups; i) decrease ankle plantarflexors average joint stiffness and increase joint energy (i.e. area under the torque-angle curve) during slow passive stretching; j) decrease antagonist muscle electromyography (EMG) during maximal voluntary isometric and concentric plantarflexion and dorsiflexion; k) not change spinal mechanisms related to hyperreflexia in the Sol muscle (i.e. Hoffmann-reflex (H-reflex), post-activation depression (PAD) ratio, tonic stretch reflex threshold (TSRT)); l) increase amplitude of cortical responses to proprioceptive stimulation, recorded with magnetoencephalography (MEG) in the primary somatosensory cortex; m) increase cortico-muscular coherence between cortical MEG and TA EMG signals; n) increase intramuscular coherence within TA muscle during a submaximal isometric dorsiflexion and during the swing phase of the gait cycle. No changes in any of the studied variables are expected during the 3-months control period, except if the participant is going through the growth spurt. After the 3-month maintenance period, the values of the studied variables are expected to be in between the control and post intervention values (project aim B). All study variables are hypothesized to show differences between the TD and CP groups (project aim C). It is expected that the comprehensive assessment battery of neuromuscular, brain, cardiometabolic and functional parameters will add valuable information about how people with CP adapt to exercise.

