
#### Electromyography

Three EMG setups will be utilized in the project. The first setup will be used for the strength, ankle flexibility and neural tests (i.e. H-reflex, PAD and tonic stretch reflex threshold). EMG activity will be recorded from Sol, MG and TA muscles with self-adhesive electrodes (Blue Sensor N, Ag/AgCl, 0.28 cm^2^; Ambu, Ballerup, Denmark), and a ground electrode placed on the tibia. Electrode placement and skin preparation will be performed according to SENIAM [85]. The electrodes will be placed on the muscle belly in accordance with the underlying fiber direction (20-mm-interelectrode distance). EMG signals will be amplified and high-pass filtered (1000X, 10 Hz) by a preamplifier (NL824; Digitimer, Welwyn Garden City, UK) and then band-pass filtered (10 Hz to 1 kHz) by a differential amplifier (NL900D/NL820A; Digitimer Ltd., UK). The signals will be acquired on a personal computer at a rate of 5 kHz via a 16-bit A/D converter (CED power 1401; Cambridge Electronics Design, Cambridge, UK). EMG during the maximal voluntary plantarflexion and dorsiflexion trials will be quantified in 200 ms root mean square (RMS) windows preceding the joint angles of 0°, 5.5°, 11°, 16.5°, 22° and 27.5°. TA coactivation during plantarflexion will be expressed as % of the maximal RMS EMG obtained on the dorsiflexion trial at the same joint position. The same procedure will be performed to express Sol and MG coactivation during ankle dorsiflexion.

The second setup utilizes a wireless EMG system (Noraxon, Scottsdale, USA) that will acquire EMG activity during the instrumented gait analysis. Data acquisition configuration, muscles tested, and electrode placement are identical to setup 1, except for two differences: 1) sampling frequency is 1.5 kHz; 2) two sets of bipolar electrodes will be placed in TA muscle, 8–10 cm apart depending on the subject’s tibia length.

The third EMG setup is built-in the MEG System (Elekta Neuromag TRIUX, Elekta Oy, Helsinki, Finland). The same bipolar electrode placement as in setup 2 will be utilized, with a MEG compatible electrode (Neuroline 720, Ag/AgCl, 0.28 cm2; Ambu, Ballerup, Denmark). EMG signal will be sampled at 1 KHz and band-pass filtered 1–1000 Hz.

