Frequency domain analysis of the EMG will be performed in the following conditions: A) intramuscular TA coherence during the swing phase of gait; B) cortico-muscular and intramuscular TA coherence during a sustained isometric ankle dorsiflexion. Condition A will be collected with EMG setup 2, during the instrumented gait analysis test (S2), and B will be collected in the MEG session (S3), using EMG setup 3. Surface EMG will be preprocessed using full-wave rectification as it has been shown to be appropriate for low force muscle actions [90–92]. The finite Fourier Transform using the method of disjoint sections will be utilized [93], in which the complete EMG record R (i.e. approximately 60 s for A, and 480 s for B) is divided in L non-overlapping disjoint sections of length T, where R = LT. For A, T will be selected to reach a spectral resolution ≤5 Hz. If possible, the swing phase will be divided into two or three parts, depending on the actual length of these phases and the achieved frequency resolution. For B, R = 480 s and T = 1 s, yielding a frequency resolution of 1 Hz. The coherence between two rectified EMG signals (x and y) is defined as their cross-spectrum normalized by the auto-spectra for a given frequency (λ), according to the following equation:
$$ {\left|{R}_{xy}\left(\lambda \right)\right|}^2=\frac{{\left|{f}_{xy}\left(\lambda \right)\right|}^2}{f_{xx}\left(\lambda \right){f}_{yy}\left(\lambda \right)} $$

Coherence measures how closely two signals are related by a linear transformation [93, 94], providing a bounded and normative measure of association, taking values between 0 and 1. A perfect linear relationship has a value of 1, while full independence has a value of 0. Pooled coherence estimates will be calculated to characterize both control and experimental groups [95]. The estimation of pooled coherence joins separate signals from different subjects into a single longer signal, and then calculates the coherence of this record using the periodogram approach. Pooling the EMG signal of different participants may result in a non-constant standard deviation (i.e. nonstationarity) between the different sections, in this case signals will be normalized to have unit variance [96].

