##### Data analyses

All further analyses of the MEG data will be processed and analyzed with the MNE-Python software package. The data will be averaged across proprioceptive stimuli in order to examine the passive-movement-evoked fields, and the respective modulation of the rhythmic activity in primary sensorimotor cortex at alpha, beta and possibly also at gamma frequency bands. Cortico-muscular and intramuscular coherence for TA will be computed as described in the EMG section. Resting state data will be analyzed with a special focus on the sensorimotor cortical network. Torque steadiness during the 8 min of submaximal effort will be calculated utilizing the standard deviation and coefficient of variation.

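### Plantarflexion recordings allowed as a fallback in the MEG isometric task cannot supply the planned tibialis anterior coherence, and nothing keeps a participant on one task across visits

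*Protocol article*

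**What the plan says.** All places are in the Protocol article.

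- **MEG protocol.** The third task is four sets of 120 s of isometric dorsiflexion at 10% of maximum. It has one exception: "If the participant is unable to perform dorsiflexion adequately, plantarflexion will be used". No criterion for adequate performance is given, and nothing is said about keeping the same task at later visits.
- **Neural parameters.** The coherence outcome for this task is "B) cortico-muscular and intramuscular TA coherence during a sustained isometric ankle dorsiflexion".
- **Data analyses (MEG).** "Cortico-muscular and intramuscular coherence for TA will be computed as described in the EMG section". There is no variant for plantarflexion.
- **Study purpose.** The hypotheses are "m) increase cortico-muscular coherence between cortical MEG and TA EMG signals" and "n) increase intramuscular coherence within TA muscle during a submaximal isometric dorsiflexion". Hypothesis n also covers the swing phase of gait, which this point does not touch.
- **Electromyography.** In setup 2, "two sets of bipolar electrodes will be placed in TA muscle". Setup 3, used in the MEG session, takes over that placement. Soleus and medial gastrocnemius are recorded too, but no second pair is described for them.

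**The concern.** The fallback changes the task, but the outcome stays the same. In dorsiflexion TA is the agonist. In plantarflexion it is the antagonist, and the Electromyography section itself treats TA activity there as coactivation. TA coherence from the two tasks is not one quantity measured twice.

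The study relies on participants serving as their own controls, so the measurement must be the same at each visit. The dorsiflexors are trained in the intervention. Someone who cannot manage the dorsiflexion task at a pre-test may manage it at post-test 1, the visit at which m and n predict a rise. The mixed model in Statistical analyses compares time points and names no task factor.

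The pooled coherence estimate raises the same issue, because it joins recordings from different participants into one record. If those recordings are scaled to unit variance, as the plan allows, an antagonist signal would get the same weight as an agonist signal. Torque steadiness over the 8 minutes of submaximal effort depends on the task as well.

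**Working it through.** **1. The plan's own figure.** Neural parameters gives a record of 480 s in 1 s sections, with 1 Hz resolution. From MEG protocol, 4 × 120 s = 480 s. The number of sections is 480 / 1 = 480, and the resolution is 1 / 1 s = 1 Hz. The figures agree, and the error is not there.

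**2. Can a plantarflexion recording give the planned parameter?**

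| Planned quantity | What it needs | What a plantarflexion recording offers |
|---|---|---|
| TA cortico-muscular coherence (m, condition B) | MEG and TA EMG during dorsiflexion | MEG and TA EMG with TA as antagonist |
| TA intramuscular coherence (isometric part of n, condition B) | Two TA pairs during dorsiflexion | Two TA pairs with TA as antagonist |
| Plantarflexor cortico-muscular coherence | MEG with soleus or medial gastrocnemius EMG | Recorded, but no such outcome is planned |
| Plantarflexor intramuscular coherence | Two pairs on one plantarflexor | Not available with the described placement |

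The first two rows fail on the definition. The third is feasible but is a different parameter. The fourth is not feasible. Hypothesis m does not itself name the task, but condition B, which defines how its coherence is obtained, does.

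**3. Can the task change between visits?** MEG is recorded at pre-test 1, pre-test 2 and post-test 1; post-test 2 has no MEG session. The fallback is conditional on ability, the trained muscles include the dorsiflexors, and no sentence holds the task fixed. A change is therefore possible. The documents do not say that it happens.

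**4. How large could the effect be?** The documents give neither the number of participants who would change task nor the difference in TA coherence between tasks, so this is illustration only. Suppose k of 24 participants do plantarflexion at the pre-tests and dorsiflexion at post-test 1, TA coherence differs by d between tasks, and there is no training effect. Then

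shift in mean change = k × d / 24.

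- k = 1, d = 0.02: 1 × 0.02 / 24 = 0.0008
- k = 2, d = 0.05: 2 × 0.05 / 24 = 0.0042
- k = 4, d = 0.05: 4 × 0.05 / 24 = 0.0083
- k = 6, d = 0.10: 6 × 0.10 / 24 = 0.025

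If d were negative, the shift would have the opposite sign. For scale, the usual 95% limit for independence in a single record of 480 sections is 1 − 0.05^(1/479) = 0.0062. That limit applies to one record and is not a standard error for a group mean, so it does not show whether such a shift would matter.

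**5. What exclusion would cost.** Dropping k = 1 to 6 participants from the TA analysis leaves 24 − 1 = 23 to 24 − 6 = 18.

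**The case against.** The strongest reply is that no harmful analysis is actually planned. Condition B is defined during dorsiflexion, so on a literal reading a plantarflexion recording is simply missing for m and the isometric part of n. No sentence puts antagonist TA coherence into the time model or the pooled estimate. An article may leave such handling rules to a fuller document.

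Part of this stands: bias needs both a change of task and inclusion of the plantarflexion recording, and the text states neither. It does not remove the point. The article states the substitution, the parameter and the analysis instruction, and they do not fit together. Followed as written, the fallback either yields data with no matching outcome or puts a different quantity under the same name.

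Three stronger readings are tempting but unsupported:

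- **That the task is chosen afresh at each recording.** The sentence is worded by participant, and one stable choice per participant fits it equally well. The text only fails to prevent a change.
- **That antagonist TA coherence is near zero, so a switch must mimic the predicted increase.** No coherence value is given. Hypothesis j expects antagonist activity large enough to reduce. That concerns maximal efforts and does not settle what TA does at 10% of maximum, so size and direction both stay open.
- **That the difference between the cerebral palsy (CP) and typically developing (TD) groups is exaggerated.** This would require plantarflexion recordings to enter that comparison, which the text does not say.

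It is also fair that a target of 10% of the participant's own maximum may leave few people needing the fallback.

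**Conclusion.** The point holds as a mismatch between a stated task rule and a stated outcome. Plantarflexion recordings cannot supply TA coherence during dorsiflexion, whatever the number of participants concerned. This conclusion needs no numerical assumption.

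The confusion of a task change with a training effect is a risk that the text leaves open. Its size and direction are unknown; the range of 0.0008 to 0.025 in the illustration rests wholly on assumed inputs.

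The scope is limited to hypothesis m, the isometric part of n, and the pooled and CP–TD versions of those estimates, with torque steadiness sharing the dependence on task. The six-minute walk primary outcome and the sample size are unaffected. The correction is cheap and should be made, but it does not bear on the main conclusion of the trial.

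**What to change.** - **Task rule.** For participants with MEG visits still to come, keep the task used at pre-test 1 at every MEG visit. This cannot reach sessions already recorded; recruitment has run since May 2017.
- **Analysis set, all participants.** Compute TA cortico-muscular and isometric TA intramuscular coherence from dorsiflexion recordings only, including the pooled estimates and the CP–TD comparisons. Use a within-participant comparison only where both visits had the same task.
- **Plantarflexion recordings.** Report them separately, using cortico-muscular coherence with soleus or medial gastrocnemius, outside hypotheses m and n. State how many participants and visits used the fallback.
- **TD group.** Leave its task as dorsiflexion. Moving a matched control to plantarflexion would lose that control's dorsiflexion data.

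The cost is a sentence or two plus an analysis-set rule, and a few participants leave the TA coherence analysis. The TA results would then describe those able to do the dorsiflexion task. Study design defers data analysis, apart from the flexibility tests, until collection is complete, so the rule can still be fixed without sight of the coherence results if it is written before then.

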##### MEG data preprocessing

First, visual data inspection will be performed to identify bad channels and periods with intense noise. Maxfilter (ver. 3.0, Elekta Neuromag Oy, Helsinki, Finland) with spatiotemporal signal space separation method [118] will be used to reduce endogenous and exogenous sources of noise in the MEG signals. Additionally, MaxFilter will be utilized for head movement compensation during MEG recording and to align the head coordinates across the different longitudinal recording sessions (pre-tests 1 and 2, and post-test 1). The coordinate transformation will be done to the participant individual mean reference head position within each MEG task separately. Artifacts caused by eye movements and cardiac activity will be identified and removed using the electro-oculograms and electrocardiography signals in combination with independent component analysis implemented in MNE-Python software package [119, 120].

##### Data analyses

All further analyses of the MEG data will be processed and analyzed with the MNE-Python software package. The data will be averaged across proprioceptive stimuli in order to examine the passive-movement-evoked fields, and the respective modulation of the rhythmic activity in primary sensorimotor cortex at alpha, beta and possibly also at gamma frequency bands. Cortico-muscular and intramuscular coherence for TA will be computed as described in the EMG section. Resting state data will be analyzed with a special focus on the sensorimotor cortical network. Torque steadiness during the 8 min of submaximal effort will be calculated utilizing the standard deviation and coefficient of variation.

